### Intervention

The MEDIA group will receive a “keeping in touch” intervention involving the SMS. The patient will receive 6 SMS items during 6 months after the SA, the first one 7 days after the SA and the last one at 6 months (Fig. 1).

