### Primary outcome analysis

To identify differences in SA recurrence, a time-to-event analysis with Cox regression modeling will be used. The study period will be up to 12 months after the SA of inclusion. Patients without another SA, who die, or who are lost to follow-up will be censored. Patients with and without an SA during the study period will be compared between the MEDIA and CLASSIC groups. Factors associated with SA recurrence will be compared by log rank test, with *p* < 0.05 considered statistically significant. Cox proportional hazards modelling of SA recurrence will include sex, group and other variables with *p* < 0.2 on univariate analysis (i.e., explanatory variables). The score obtained from the CES-D at the time of inclusion will be considered an explanatory variable. This method will allow for considering a confusion factor and determining which initial characteristics are significant risk factors for recurrence of SA. Hazard ratios (HRs) and 95 % confidence intervals (95 % CIs) will be calculated to indicate the probability of SA recurrence by characteristics entered in the model. We will test for interactions between the included variables. Each variable will be checked for proportionality assumption by a graphical method and the Moreau method, and variables not meeting proportionality will be used for stratification [36].

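### The rule that turns any non-proportional variable into a stratification factor does not exempt treatment group; applied to group, it would remove the treatment hazard ratio from the primary Cox analysis

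*Protocol article*

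**What the plan says.** All the relevant statements on the model are in the protocol article under Primary outcome analysis.

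- Method: "a time-to-event analysis with Cox regression modeling will be used".
- Content of the model: "Cox proportional hazards modelling of SA recurrence will include sex, group and other variables with *p* < 0.2 on univariate analysis". Group is therefore listed as one of the model's variables.
- Check: "Each variable will be checked for proportionality assumption by a graphical method and the Moreau method".
- Consequence of failing it: "variables not meeting proportionality will be used for stratification".
- Effect measure: HRs with 95 % confidence intervals, which "will be calculated to indicate the probability of SA recurrence by characteristics entered in the model".
- Separate univariate step: "Factors associated with SA recurrence will be compared by log rank test". The section also plans to compare the two arms on patients with and without a recurrence.

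On timing, the Intervention section says "The patient will receive 6 SMS items during 6 months after the SA", with the last message at month 6. The primary analysis looks further: "The study period will be up to 12 months after the SA of inclusion".

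**The concern.** Stratifying on a variable that fails proportional hazards is ordinary practice for a nuisance covariate. It works because nobody needs that covariate's coefficient. Treatment group is different, because its coefficient is the result of the trial. As written, the rule makes no distinction between the two.

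The circumstance that would trigger it is not remote. The intervention stops halfway through the observation period, so an effect that fades after the last message is an obvious alternative to a constant HR. If group were then flagged, the analyst would face two poor options. Following the text would leave the primary model without a treatment estimate. Departing from it would mean choosing a replacement after seeing the data, in what the Statistical method section presents as the confirmatory analysis.

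**Working it through.** The plan gives no figure for this point, so there is none to reproduce. The check has two parts: what stratifying on group does to the model, and how often the rule might be triggered.

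**1. Stratifying on group removes its coefficient.** In a stratified Cox model, the patient *i* who has an event contributes

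exp(β·g_i + γ'x_i) / Σ_j exp(β·g_j + γ'x_j),

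where the sum runs over patients still at risk in the same stratum. If the stratum is group, every g_j in the sum equals g_i. The factor exp(β·g_i) cancels, and β is no longer in the likelihood.

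This was confirmed on one simulated trial. It had 224 patients (2 × 112, from Sample size calculation), censoring at 12 months, a baseline hazard giving 30 % recurrence at 12 months and HR 0.66. Sex and a depression score were covariates with assumed effects.

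| Group coefficient tried | Log-likelihood, group as covariate | Log-likelihood, group as stratum |
|---|---|---|
| -2 | -373.1 | -308.098 |
| -0.4155 (= ln 0.66) | -354.2 | -308.098 |
| 0 | -355.3 | -308.098 |
| 1 | -369.4 | -308.098 |

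- Group as covariate: log-HR -0.377, SE 0.246. The HR is exp(-0.377) = 0.69, with 95 % interval exp(-0.377 ± 1.96 × 0.246) = 0.42 to 1.11.
- Group as stratum: score and information for group are zero to rounding. No HR, interval or test for group exists in that model; only the covariate coefficients remain.

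**2. How often group might be flagged.** Inputs from Sample size calculation are 224 patients, 30 % control recurrence at 12 months and 10 % loss. With a constant HR of 0.66, the experimental arm's 12-month risk is 1 - 0.70^0.66 = 0.210. Expected events before loss are 224 × (0.300 + 0.210)/2 = 57.

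The period-specific HRs and the shape of the hazard over time are assumptions, because the article gives neither. Most figures come from a score-type test of group by rank event time at the 5 % level, with 3,000 trials per scenario in the runs at constant HR and at 0.5 then 1.0. That test stands in for the one the article names. The ranges cover separate runs and different hazard shapes.

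| HR months 0-6, then 6-12 | Group flagged, rank-time test | Group flagged, two-period test split at month 6 |
|---|---|---|
| constant | about 4-5 % | not run |
| 0.66, then 1.0 | about 8-9 % | about 12 % |
| 0.5, then 1.0 | 13-14 % (early-concentrated hazard); 20 % (half of the hazard in months 6-12) | about 22-26 % |

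Under waning, then, a rank-time test flags group in roughly 8 to 20 % of trials, and a test aimed at the month-6 change flags it somewhat more often. The graphical check has no stated threshold, so its contribution cannot be quantified.

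**The case against.** **The authors probably meant covariates only.** The section attaches the term explanatory variables to the covariates. Secondary outcomes analysis sets such variables apart from the two arms being compared. This may well be the intent. The text does not say so, however, and the list of model terms places group among the variables.

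**The trial would still have an answer.** A reader might infer that the rule leaves the primary question unanswered. The document does not support that. The loss is confined to the Cox model: the log-rank test and the comparison of patients with and without a recurrence are untouched, so the arms can still be tested against each other. What goes is the adjusted HR and its interval. Neither surviving comparison is designated as the primary result in that case, and the log-rank test gives a p-value without an effect size.

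**The flag rate could be made to look much larger.** If the HR went from 0.5 to 1.5, rank-time tests flagged group in about 31 to 43 % of simulated trials, depending on the hazard shape. That requires harm after the messages stop, which nothing in the document suggests, so it should not be the headline. Even 0.5 in months 0-6 is stronger than the planned 0.66. With 0.66 then 1.0, the rank-time rate is only 8 to 9 %.

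**A fallback analysis belongs in the statistical analysis plan.** Agreed, and its absence from a condensed article is not the finding. The finding is the unrestricted wording of a rule that the article does state.

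**Conclusion.** The point holds in limited form. Taken literally, the proportionality rule covers treatment group. Applying it there would remove the treatment HR and confidence interval, the only effect measure named for the primary Cox analysis. This follows from the algebra of the model and needs no assumption.

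How often it would matter does rest on assumptions. It is about 5 % under true proportionality and roughly 8 to 20 % under the assumed waning with a rank-time test. These figures depend on the chosen period HRs, the hazard shape and a stand-in for the named test. If group is not flagged, this rule does not affect the treatment estimate.

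This should be fixed, because the remedy is nearly free. It does not invalidate the design.

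**What to change.** Limit the stratification rule to covariates other than group. State that group always stays in the primary Cox model as a term, and that the primary test is the same whatever the proportionality check shows. Making the primary conclusion switch to another test after a proportionality test would be a data-driven choice and is better avoided.

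If group appears non-proportional, report as supplementary results either the HRs for months 0-6 and 6-12 or the difference in restricted mean recurrence-free time to 12 months. The primary HR should then be described as an average over follow-up.

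The cost is a sentence or two and one extra analysis in SAS. Sample size and data collection do not change. The Ethics and permissions section describes inclusions as not yet begun, so at that stage the wording could be settled before any outcome data existed.

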### Secondary outcomes analysis

The weight of the explanatory variables on SA recurrence will be compared between the MEDIA and CLASSIC groups; the log-rank test will be used for comparing the time of SA recurrence between the groups for each explanatory variable. The groups will be compared for scores obtained with the MSPSS, Kidscreen-27 and VSP-A questionnaires.

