## Sample size calculation

The sample size of this study was calculated by using data from earlier studies [4, 5]. With one control per experimental subject, an accrual interval of 18 months, and additional follow-up after the accrual interval of 12 months, an alpha risk of 5 % and power of 80 %, assuming 30 % SA recurrence in the first year after an SA and median SA recurrence at 3 months, and an estimated hazard ratio of 0.66, we will need 92 subjects in each group. Assuming 10 % lost to follow-up, we will aim to enroll 112 subjects in each group. This sample size was calculated by using Power Sample Size v3.0.43 for Windows.

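### The secondary analysis asks whether each variable's weight on recurrence differs between arms, but the log-rank test it names does not test that and is not tied to the interaction tests planned for the Cox model

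*Protocol article*

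**What the plan says.** The Secondary outcomes analysis section of the protocol article states the question: "The weight of the explanatory variables on SA recurrence will be compared between the MEDIA and CLASSIC groups". In the same sentence, after a semicolon, it gives the method: "the log-rank test will be used for comparing the time of SA recurrence between the groups for each explanatory variable". It names no other method for this comparison and does not point to another section.

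Two other sections bear on the point:

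- **Primary outcome analysis** describes a Cox model that always contains sex and group, plus variables passing a univariate screen at p < 0.2. It calls these the explanatory variables, names the inclusion CES-D score as one of them, and plans to test interactions among the variables in the model. It does not single out group-by-variable terms.
- **Statistical method** sets significance at P < 0.05, makes no multiplicity adjustment for secondary analyses, and describes them as supplementing the confirmatory primary analysis.

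**The concern.** Whether a variable weighs differently on recurrence in the two arms is a question of effect modification. It needs a test of the difference between two effects. The log-rank sentence can be read in three ways, and none supplies that test:

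- **MEDIA against CLASSIC within each level of a variable.** This gives one p-value per level and no test of whether the levels differ.
- **Each variable tested within each arm.** This gives one p-value per arm and no test of whether the arms differ.
- **MEDIA against CLASSIC stratified by each variable.** This gives one pooled treatment comparison and removes the contrast of interest.

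A log-rank test also needs the CES-D score cut into categories, whereas a Cox model can take it as it is.

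The risk is a subgroup claim, that SMS works in one kind of adolescent and not another, resting on one p-value below 0.05 and one above it. The protocol would also hold two analyses that bear on one question, log-rank tests by variable and Cox interaction terms, with no statement of which one answers it.

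**Working it through.** **Inputs.** From the Sample size calculation: "an estimated hazard ratio of 0.66"; "an alpha risk of 5 % and power of 80" per cent (two-sided assumed, since sidedness is not stated); "With one control per experimental subject"; "assuming 30 % SA recurrence in the first year after an SA and median SA recurrence at 3 months"; "an accrual interval of 18 months, and additional follow-up after the accrual interval of 12 months"; 92 per group before losses and 112 after. From the Primary outcome analysis: "The study period will be up to 12 months after the SA of inclusion". Further assumptions: exponential times, a two-level variable, and no losses in the event counts.

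**Step 1: the plan's own figure.** Schoenfeld's formula gives events = 4(1.960 + 0.842)² / (ln 0.66)² = 182, or 90.9 per group if every patient had an event. With accrual A = 18, follow-up F = 12 and hazard λ = ln 2 / median, the event probability is 1 − [exp(−λF) − exp(−λ(A+F))]/(λA). It is evaluated at the average of the two medians.

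- Medians 3 and 3 × 0.66 = 1.98 months: probability 0.993, so 90.9/0.993 = 91.6, or 92 per group.
- Medians 3 and 3/0.66 = 4.55 months: probability 0.968, so 90.9/0.968 = 93.9, or 94 per group.

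The stated 92 therefore corresponds to about 182 events, with a 3-month median applied to all patients.

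**Step 2: events if 30% recur in one year.** The MEDIA proportion is 1 − 0.70^0.66 = 0.210.

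- 92 per group: 92 × (0.300 + 0.210) = 46.9 events.
- 112 per group: 112 × (0.300 + 0.210) = 57.1 events.

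The section supports both this count and the one in step 1, so both are carried forward.

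**Step 3: discordance when the true effect is the same in both levels.** With d events in a level, two-sided power is Φ(√(d/4) × 0.4155 − 1.96) + Φ(−√(d/4) × 0.4155 − 1.96), where 0.4155 = |ln 0.66|. With powers a and b in the two levels, exactly one is significant with probability a(1 − b) + b(1 − a).

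| Total events | Split of events | Power by level | Exactly one significant |
|---|---|---|---|
| 46.9 | 50/50 | 0.172, 0.172 | 0.284 |
| 46.9 | 30/70 | 0.122, 0.222 | 0.289 |
| 57.1 | 50/50 | 0.199, 0.199 | 0.318 |
| 57.1 | 30/70 | 0.138, 0.259 | 0.326 |
| 182 | 50/50 | 0.509, 0.509 | 0.500 |
| 182 | 30/70 | 0.336, 0.650 | 0.549 |

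If SMS has no effect in either level, the figure is 2 × 0.05 × 0.95 = 0.095.

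**Step 4: simulation, 5,000 trials per scenario.** The interaction test here compares the two level-specific log hazard ratios estimated from the log-rank statistics. It approximates the Cox term and is not a fitted Cox model.

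| Scenario | Mean events | Discordance | Interaction test, p < 0.05 |
|---|---|---|---|
| 30% at 12 months, 92 per group, 50/50 | 47.0 | 0.281 | 0.047 |
| 30% at 12 months, 112 per group, 50/50 | 57.1 | 0.308 | 0.049 |
| 30% at 12 months, 112 per group, 30/70 | 56.9 | 0.313 | 0.047 |
| As above, 50/50, HR 1 in both levels | 67.3 | 0.100 | 0.053 |
| Median 3 months, 92 per group, 21 months' follow-up, 50/50 | 179.6 | 0.498 | 0.067 |
| Median 3 months, 92 per group, 21 months' follow-up, 30/70 | 179.5 | 0.556 | 0.068 |
| Median 3 months, 92 per group, 12 months' follow-up, 50/50 | 163.5 | 0.503 | 0.062 |

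The simulation agrees with the formula. Restricting the 3-month-median scenario to the 12-month analysis window leaves the discordance at about 50%.

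**The case against.** The strongest reply is that interaction testing is already planned. The Primary outcome analysis tests interactions among the Cox model's variables, group is always one of them, and its explanatory variables are the ones the secondary section refers to. Group-by-variable terms therefore fall within the plan. This stands, and it limits the point. A reader might infer that log-rank tests are the protocol's only means of judging effect modification, and the documents do not support that. What remains is that the secondary section attaches a different test to the between-arm comparison and never invokes those terms.

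A reader might also infer that the plan will declare a subgroup difference whenever one level is significant and the other is not. No section states such a rule. The sentence invites that reading because it offers nothing else, but the 28–55% range applies only if the p-values are contrasted in that way. It does not apply to a stratified log-rank test, which gives no level-specific p-values.

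Finally, a reader might add up the tests and quote a high chance of at least one p < 0.05. The number of explanatory variables is not fixed, and tests on different variables reuse the same patients, so no such figure can be derived. It would in any case measure ordinary multiplicity, which the protocol openly leaves unadjusted for supportive analyses and which interaction tests share.

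**Conclusion.** The point holds in this limited form: for its own question, the secondary section names a test that does not answer it, and it leaves unused the interaction tests planned one section earlier. If within-level p-values were contrasted, identical effects would look different in about 28–33% of trials at 47–57 events and about 50–55% at 182 events, against about 5–7% for a direct interaction test of one variable.

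These figures rest on two-sided 5% tests, exponential times, a constant hazard ratio of 0.66, a two-level variable split 50/50 or 30/70, and no losses. Taking 10% losses from 112 gives 101 patients and about 51.5 events per 101 in each group, which lies inside the first range. The primary comparison is unaffected, and the analysis concerned is declared supportive. It is still worth correcting, because the wrong method is stated rather than left open.

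**What to change.** In the Secondary outcomes analysis, state that the between-arm comparison of each variable's weight rests on the group-by-variable interaction term in the Cox model of the Primary outcome analysis, with CES-D entered as a continuous score. For each variable, report the ratio of hazard ratios and the level-specific hazard ratios, with 95% confidence intervals. For CES-D, give the hazard ratio at chosen scores in place of levels. Keep any level-specific log-rank results or survival curves as description only.

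The cost is a change of wording: no new data, patients or model. Two limits remain. Interaction tests have low power at these event counts, so a non-significant term is not evidence that effects are equal. Some multiplicity also remains without adjustment: if the tests were independent, 3, 5 or 8 of them at 5% would give at least one false positive with probability 1 − 0.95³ = 14%, 1 − 0.95⁵ = 23% or 1 − 0.95⁸ = 34%. The results should therefore keep the supportive status that the Statistical method section gives them.

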## Methods/Design

### Aims and hypothesis

We hypothesized that the SMS sent over a 6-month period after an SA, in addition to usual care, may increase the delay in SA reccurence. Therefore, the primary objective is to determine whether, as compared with usual care, SMS in addition to usual care can be used to keep in touch with adolescent suicide attempters to reduce the delay in recurrence of an SA. A secondary hypothesis is that the SMS received after a first SA will reduce the suicide rate.

Secondary objectives are to determine whether, as compared with usual care, SMS in addition to usual care can be used to keep in touch with adolescent suicide attempters to improve the evolution of 1) their social network, 2) depression and 3) health-related quality of life.

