**Fig. 1 Fig1:**
[figure not shown]
Design of the MEDIACONNEX study. Legends: D = day; M = month; SA = suicide attempt; SMS = short message service

The first SMS will be sent soon after the SA because studies of adult suicide attempters underline the importance of an early start for connectedness measures.The SMS for this purpose was developed in a focus group of peers and adolescents. A pilot study was carried out in 2015 (MEDIADO, manuscript submitted) to refine the content of the SMS. The SMS item will be sent automatically from a computerized program and will change over the follow-up. The items will be personalized with the surname and genre of the patient and name of the psychiatrist or the immediate superior who meets the patient after the SA. The phone number of the unit will be included in the message and patients will be encouraged to call whenever they need to. The message will specify that someone will be always present for the patient.

Participants of both groups (MEDIA and CLASSIC) will receive usual care, and 4 self-reports will be completed by participants, at inclusion and at 6 months, to evaluate the evolution of the scores for perception of the social network (Multidimensional Scale of Perceived Social Support [MSPSS]), health-related quality of life (Kidscreen-27; Vécu et Santé Perçue des Adolescents [VSP-A]) and mood disorder (Center for Epidemiologic Studies Depression Scale [CES-D]).The MSPSS is a 12-item self-reporting questionnaire related to the participant’s social network with 5 possible answers for each item. It assesses perceptions of social support from family members, friends, and significant others. It has been used in other countries [29, 30] and was translated and validated in French by a team in Toulouse [31]. The 3 subscales, each addressing a different source of support, were identified and found to have strong factorial validity. The MSPSS had also a good internal and test–retest reliability and moderate construct validity. High levels of perceived social support are associated with low levels of depression and anxiety.

The Kidscreen-27 is a 27-item self-reporting health-related quality-of-life questionnaire developed by a European group [32] and validated in 12 European countries. It evaluates physical wellness, psychological wellness, relationships with parents, the social network, relationships with friends, and schooling. The internal consistency is good and the instrument has good discriminating power.

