### Outcomes

The primary outcome will be the delay of SA recurrence during 12 months after inclusion in the study. The SA recurrence and date of occurrence will be collected by a member of the research team in each participating hospital.

Secondary outcomes will include evaluation and evolution for 6 months after the SA of the adolescent’s social network by using the MSPSS, health-related quality of life by using Kidscreen-27 and VSP-A, and depression by using the CES-D. The scores and their evolution will be compared between CLASSIC and MEDIA groups.

Finally, the entire process will be evaluated by a short self-report at 6 months after the SA.

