## Statistical method

The primary analyses will be conducted on an intent-to-treat basis with data for all randomised participants. A per-protocol analysis of the primary outcome, adjusted on center, will also be reported. Continuous variables will be described with mean (SD) or median (range) and categorical variables with number (%), as appropriate. The chi-square or Fisher exact test will be used for analysis of qualitative variables and Student *t* or Mann–Whitney test for quantitative variables.

Differences in primary and secondary outcomes between the 2 groups will be tested independently. No formal adjustments will be used to constrain the overall type I error associated with the secondary analyses. Secondary analysis aims to supplement evidence from the confirmatory primary analysis, and results will be interpreted in this context.

Data will by analyzed by using SAS 9.3 for Windows (SAS Inst., Cary, NC). *P* < 0.05 will be considered statistically significant.

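### The secondary scales have no baseline-adjusted analysis although each is measured at inclusion, which costs precision, and the CES-D is missing from the sentence listing the scores to be compared

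*Protocol article*

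**What the plan says.** All references are to the protocol article.

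- **Aims and hypothesis:** the secondary objectives are "to improve the evolution of 1) their social network, 2) depression and 3) health-related quality of life". The abstract likewise lists depression among the secondary endpoints.
- **Intervention (text after Fig. 1):** in both groups, "4 self-reports will be completed by participants, at inclusion and at 6 months, to evaluate the evolution of the scores". The four instruments are the MSPSS, Kidscreen-27, VSP-A and CES-D.
- **Outcomes:** after the MSPSS, the secondary outcomes continue with "health-related quality of life by using Kidscreen-27 and VSP-A, and depression by using the CES-D". The section then states: "The scores and their evolution will be compared between CLASSIC and MEDIA groups".
- **Statistical method:** a general sentence assigns "Student *t* or Mann–Whitney test for quantitative variables". No other method for quantitative variables is named. The section also declares that secondary analyses supplement the primary one and carry no multiplicity adjustment.
- **Secondary outcomes analysis:** "The groups will be compared for scores obtained with the MSPSS, Kidscreen-27 and VSP-A questionnaires". No test is named for the scores, and the CES-D is not listed.
- **Primary outcome analysis:** "The score obtained from the CES-D at the time of inclusion will be considered an explanatory variable", that is, in the model for recurrence. This is the only mention of the CES-D in the statistical text.

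**The concern.** Two things look wrong.

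First, each scale has a value at inclusion and one at 6 months, yet the only tests on offer are two-sample tests without covariates. Applied to the 6-month score, such a test ignores the baseline. Applied to the change, it uses the baseline but gives it a fixed weight of one, which is too much whenever the correlation between the two visits is below 1 (equal variances). Doing both gives two results per scale, and nothing in the analysis sections says which one answers the objective if they differ.

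Second, depression is one of three numbered secondary objectives, but the sentence governing the secondary analysis names three of the four questionnaires and leaves out the one that serves it. Someone programming from the statistical sections alone would use the CES-D as a predictor of recurrence and might never compare its 6-month value between groups.

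At stake are the precision and clarity of the supportive analyses. The primary time-to-event analysis is not touched.

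**Working it through.** **Precision**

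The protocol states no SD, effect size, correlation or power for the secondary scores, so there is no figure of its own to reproduce. Inputs:

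- n = 92 per group, borrowed from the Sample size calculation section (primary outcome) only to give a scale. The variance ratios do not depend on it.
- Two-sided 5% level and 80% power. The protocol gives 5% and 80%; two-sided is my reading.
- r, the correlation between inclusion and 6-month scores within group: **assumed**, 0.3 to 0.7.
- Equal variance σ² at both visits: **assumed**.
- For the power figures, a true difference of 0.35 SD: **assumed**, for illustration.

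The variance of the estimated group difference is (2σ²/n) times a factor:

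- 6-month score alone: 1
- change score: 2(1 − r)
- ANCOVA: 1 − r² (ignoring the negligible cost of estimating the slope)

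So the ratio of ANCOVA to the 6-month score is 1 − r², and that of ANCOVA to change is (1 − r²)/[2(1 − r)] = (1 + r)/2.

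| r | ANCOVA / 6-month score | Variance cut | ANCOVA / change | Variance cut |
|---|---|---|---|---|
| 0.3 | 0.91 | 9% | 0.65 | 35% |
| 0.5 | 0.75 | 25% | 0.75 | 25% |
| 0.7 | 0.51 | 49% | 0.85 | 15% |

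The smallest difference detectable with 80% power, in SD units, is (1.96 + 0.84) × √(2/92) × √factor. For the 6-month score alone this is 0.413.

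| r | Detectable, 6-month | Detectable, change | Detectable, ANCOVA | Power at 0.35 SD, 6-month | Power, change | Power, ANCOVA |
|---|---|---|---|---|---|---|
| 0.3 | 0.413 | 0.489 | 0.394 | 66% | 52% | 70% |
| 0.5 | 0.413 | 0.413 | 0.358 | 66% | 66% | 78% |
| 0.7 | 0.413 | 0.320 | 0.295 | 66% | 87% | 91% |

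Under these assumptions ANCOVA is more precise than the 6-month comparison for any r other than 0, and than the change comparison for any r below 1. Which of the two unadjusted comparisons is better depends on whether r is below or above 0.5, which the protocol does not tell us.

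**Chance imbalance**

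Suppose the groups happen to differ by δ at inclusion. The expected 6-month difference then shifts by rδ, and the expected change difference by (r − 1)δ. At r = 0.5 these are +0.5δ and −0.5δ. The two planned comparisons are therefore pulled in opposite directions by the same imbalance. ANCOVA removes the shift.

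**CES-D**

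| Section | Depression / CES-D as an outcome? |
|---|---|
| Abstract | Yes, secondary endpoint |
| Aims and hypothesis | Yes, objective 2 |
| Intervention | Yes, completed at both visits |
| Outcomes | Yes, score and evolution compared |
| Primary outcome analysis | No, inclusion score as explanatory variable only |
| Secondary outcomes analysis | Not listed |

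Four sections agree with one another, and the list in the last row does not match them.

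**The case against.** Several objections have force.

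- **The test assignment is an inference.** The secondary analysis section names no test, and the Student t and Mann–Whitney sentence is general. A condensed article may leave the model to an analysis plan that is not shown. This stands as a caution. Still, the article does name a method for quantitative variables and offers no other for the scores, so this is the natural reading.
- **Evolution already uses the baseline.** This is true, and a reader who infers that baseline is ignored altogether goes too far. The change comparison takes it into account, only less efficiently than ANCOVA. The objectives are also worded as evolution, which hints that change is the main comparison, but the Outcomes section puts scores and evolution side by side.
- **Unadjusted tests are valid.** A reader might infer from the imbalance argument that the planned comparisons are biased. The documents do not support that. Under randomisation, chance imbalance is already reflected in the standard error and the type I error is kept. The loss is of precision, in analyses that the protocol itself calls supplementary.
- **The depression objective is not dropped.** A reader of the statistical sections alone might infer that it is. The Outcomes section, however, names the CES-D and commits to comparing its scores and evolution between groups. The fault is one missing name in one sentence.
- **The size is assumed.** No correlation is given, and at r = 0.3 the gain over the 6-month comparison is small (power 66% to 70%). This stands, which is why a range is shown.

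**Conclusion.** The point holds as a matter of efficiency and consistency, not of validity. As written, the plan offers only unadjusted comparisons of 6-month scores and of change for scales that all have a baseline value, and it fixes no single main analysis per scale. Under an assumed correlation of 0.3 to 0.7 and equal variances, ANCOVA would lower the variance by 9% to 49% against the 6-month score and by 35% down to 15% against change. The direction does not depend on the value of r within that range; the size does. Separately, the omission of the CES-D from the secondary analysis sentence contradicts four other sections and should be reconciled, although the commitment to compare it survives in the Outcomes section. The conclusion of the primary analysis is not at risk. The change is worth making because it is almost free.

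**What to change.** For each of the MSPSS, Kidscreen-27, VSP-A and CES-D, state one main analysis: the 6-month score compared between groups by ANCOVA, adjusted for the same score at inclusion, and reported as an adjusted mean difference with 95% CI. Any unadjusted comparison of scores or of change can stay as descriptive support. Add the CES-D to the list in the Secondary outcomes analysis section so that it agrees with the abstract, aims, intervention and outcomes sections. Its use as an explanatory variable in the recurrence model need not change.

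The cost is a few lines in the protocol or analysis plan. Both values of each scale are already collected, so no new data, visits or participants are needed. The article says that inclusions had yet to begin, so the wording could be settled before any outcome is seen.
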